#### Diurnal Activity

Diurnal activity indicates the activeness of a person on SM both during the daytime and at night. It has been mentioned that individuals who are depressed are most active during the night [6,30,86]. In our study, we will investigate the moods [87] of all people who have written posts on SM. We intend to determine the emotions of a person who is depressed (ie, to visualize whether the person is actually depressed).

Diurnal activity will be calculated using the following formula:

XG(d,h) / ∑XG(d,i) **(1)**

where XG (d,h) indicates the average timing of the total number of posts made in hours (h) and days (d), the G in XG indicates the country where the post was made. In addition, h indicates a value from 0 to 23 (ie, an average number of posts is considered up to 11 PM).

Another study indicates a positive relationship between the use of emojis and genders (ie, women use more emojis than men), and the most frequently used emoji was the emoji representing tears of joy, with a use percentage of 22.2% and 18.9% among women and men, respectively. However, to investigate the emoji choices of both genders, a statistical analysis was carried out, named “mutual Information” (MI), which calculates the use of emojis by both men and women [88]:

MI(X;Y)e = ∑∑P(x,y)e log (P(x,y)e) / (P(x)e × P(y)e) **(2)**

where X indicates whether the gender (either men or women) uses an emoji. Here, the value of x will be equal to 1 if a user applies emojis, and if the value of x is equal to 0, then the user does not apply emojis. However, Y indicates a user’s gender (ie, for men, the value of y will be equal to 1; for women, the value of y will be equal to 1). Here, X is represented as a member of x, and Y is represented as a member of y. In contrast, p(x,y)e indicates the joint probability of X and Y, whereas p(x)e and p(y)e indicate the marginal probability of X and Y [88].

For analyzing the data from Facebook, we will observe the time stamps for negative posts and the types of emojis that are used frequently on posts related depression. We will be focusing on the formulas given earlier, but we will adjust the variables to suit our needs.

For “negative” emotions from posts for “diurnal activity,” we will be applying the text2emotion Python function to extract the emotional words used on the posts. However, the text2emotion library shows 5 different emotions, namely happy, sad, angry, surprise, and fear. However, here, we will be dealing with the negative feelings from Facebook posts.

First, our main purpose is to clean the data to make them appropriate for analyzing emotions. For the data cleaning process, we need to follow several steps. For instance, we need to remove the unwanted texts or words from the posts (ie, the words that have low frequency based on term frequency–inverse document frequency), apply various tools of the Natural Language Toolkit for sentiment analysis, and extract the better-preprocessed posts from the previous preprocessed posts. Second, we need to figure out the emotional words from the preprocessed texts and then use them for further visualization of the emotions. Finally, we need to observe the scores of the emotions. The higher the score from 1 of the 5 categories, the more the emotion will belong to that group.

After that, we intend to observe the emojis from the posts to investigate what type of nonverbal attributes a person who is depressed has both during the daytime and nighttime while writing posts on SM. This will help us figure out which emojis a person who is depressed uses repeatedly during the night. Several studies were conducted on emojis [89-92], indicating how they coincide with the linguistic style of a person. For instance, the emojis that are inclined with the negative words from LIWC are “anger,” “money,” “ingest,” “family,” “home,” and “death” [89].

As mentioned earlier, we will be focusing on the sentiments in the posts and the frequently used emojis by an individual during nighttime. Moreover, we will be considering how the emotions in a person’s post and the number of emojis used on a post are correlated with diurnal activity. For that, we will be using the formula for MI, as it consists of both joint probability and marginal probability. “Joint probability” will help investigate the relationship between the emotions in the posts and the number of emojis used, applying a condition, that is, if we work on the sentiments in the posts, then the number of emojis will be kept constant, and vice versa. In contrast, “marginal probability” will help us extract 1 feature at a time (ie, the features will be independent of one another).

There will be a change in the formula for both *“*diurnal activity*”* and MI (ie, in the *“*diurnal activity” formula, the number of posts will be denoted as “Po,” and not XG). For MI, instead of “X” and “Y,” we will write “Po” and “E,” respectively. Here, “Po” will indicate the posts written by an individual during nighttime, and “E” will indicate the types of emojis used by that individual.

The modified formulas for diurnal activity and MI are as follows:

(Po(d,h)) / (∑Po(d,i)) **(3)**

MI(Po,E) = ∑∑P(Po,E)e log (P(Po,E)e) / (P(Po)e × P(E)e) **(4)**

To find out the MI, we will consider various combinations for the number of “negative” posts and emojis used by an individual. We will consider the values of both Po and E as binary 1 (ie, Po=1 and E=1) if the posts are “negative” and the emojis are used.

In contrast, we will consider the values of both Po and E as binary 0 (ie, Po=0 and E=0) if the posts are “nonnegative” and no emojis are used in the post.

There are other combinations as well, that is, Po=0 and E=1 if the number of posts is “nonnegative” and emojis are applied in the posts, and Po=1 and E=0 if the posts are “negative” and no emojis are used in the posts.

Here, we will eliminate Po=0 and E=1 and Po=0 and E=0, as we will not deal with “nonnegative” posts (ie, Po=0) and “zero emojis” (ie, E=0).

The highest value of MI will indicate both the number of “negative” posts and “emojis” (Po=1 and E=1) used. In contrast, the lowest value will indicate either the number of “nonnegative” posts and “emojis” (Po=0 and E=1) used or the number of “nonnegative” posts and “zero emojis” (Po=0 and E=0).

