#### Advertisement Analysis

Participants revealed a tendency to reduce their SM posts during periods of low moods, with the belief that their SM content might not accurately depict their depressive state. SM platforms such as Facebook use algorithms to direct advertisements to suitable users, leveraging search keywords and previously accessed links. A subset of participants acknowledged the practice of targeted advertising, while a minority reported posting specifically to seek support. In addition, participants acknowledged the existing use of targeted advertising and expressed a preference for its application in mental health care provisioning as opposed to its current use. Individuals experiencing depression tend to conduct searches related to health-related topics, resulting in personalized advertisements that align with their search preferences.

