## Results

Our system is anticipated to automatically detect posts related to depression by analyzing the text and use pattern of the individual with the best accuracy possible. Ultimately, our research aims to have practical utility in identifying individuals who may be at risk of depression or in need of mental health support.

Simultaneously, by analyzing daily activities on SM, we aim to determine how frequently individuals write “negative” posts on Facebook, as such posts are often associated with depression [94]. Additionally, we will examine the types of emojis that are used repeatedly by these individuals. This will help us identify how often an individual uses emojis while writing a post. Moreover, if a person does not use an emoji, their posts will be detected based on the score of their “negative” emotional words (ie, “sad,” “angry,” or “fear”).

By accurately classifying individuals based on their text analysis, we hope to contribute to the development of early detection systems or interventions that can enhance mental health screening and well-being.

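### Negative posts are timed and counted but never related to all posts, so the diurnal value and the negative-post count cannot be read as negativity

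*Protocol article*

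**What the plan says.** The Diurnal Activity section starts from a published ratio, formula (1), whose quantity XG is built on the total number of posts by hour and day. It then announces that the variables will be adapted and that "we will observe the time stamps for negative posts".

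The adapted version, formula (3), replaces XG by Po in both numerator and denominator. Po has more than one meaning in that section:
- In introducing formula (3), it stands for the number of posts.
- A few lines later it "will indicate the posts written by an individual during nighttime".
- For mutual information, formula (4), it is a binary indicator of a negative post.

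In the mutual-information step the text adds: "Here, we will eliminate Po=0 and E=1 and Po=0 and E=0", on the ground that nonnegative posts will not be dealt with.

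The Results section states the descriptive aim: "by analyzing daily activities on SM, we aim to determine how frequently individuals write" negative posts. The Advertisement Analysis section reports: "Participants revealed a tendency to reduce their SM posts during periods of low moods".

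The overview of Text and Behavior Analysis lists post time, number of posts and posting frequency as features in their own right. No section divides negative posts by all posts, either per person or within an hour band.

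**The concern.** How negative a person's posting is, and whether it is more negative at night, are both shares: negative posts out of all posts, overall or within a time band. The stated quantities have different denominators or none. A distribution of negative posts over the hours inherits the distribution of all posting over the hours. A number of negative posts inherits the person's posting volume.

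If these quantities are read as negativity, a contented night-time poster resembles someone who turns negative at night, and a withdrawn person with few but mostly negative posts can look less negative than a prolific one. The people the study wants to detect are, by the article's own account, those whose posting may fall.

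**Working it through.** The article gives no figure to reproduce on this point and no posting rates. All post numbers and negative shares below are assumptions chosen to show the mechanism.

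**Timing.** Let a be the share of a person's posts made at night, and qn and qd the shares of night and day posts that are negative. If Po is negative posts, formula (3) summed over the night hours gives

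a·qn / [a·qn + (1 − a)·qd].

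If qn = qd, this reduces to a, whatever the level of negativity:
- a = 0.60: the value is 0.60 with 10% negative and 0.60 with 60% negative.
- a = 0.20: the value is 0.20 in both cases.

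If qn and qd differ, the ranking can still follow posting time:
- User A posts 60% at night and is 30% negative at all hours: 0.18 / (0.18 + 0.12) = 0.60.
- User B posts 20% at night and is 50% negative at night, 25% by day: 0.10 / (0.10 + 0.20) = 0.333.

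Both are 30% negative overall. Only B is more negative at night (by 25 percentage points), yet B has the lower value.

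If Po is all posts, or all night posts, formula (3) contains no information on negativity. So on no reading does it give the negative share by time of day.

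**Count.** Number of negative posts = volume × negative share. With volumes V1, V0 and shares s1, s0, the expected count reverses when V1/V0 < s0/s1.
- 20 posts at 50% = 10, against 100 at 20% = 20: reversed.
- 30 at 40% = 12, against 20: reversed.
- 60 at 40% = 24, against 20: not reversed.

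A simulation used 5,000 people per group, mean shares of 40% and 20% varying between people, a mean of 100 posts in the non-depressed group and negative-binomial volumes (size 1). The AUC for the share uses people with at least one post.

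| Volume ratio, depressed / non-depressed | AUC, negative count | AUC, negative share |
|---|---|---|
| 1 | 0.67 | 0.82 |
| 0.75 | 0.61 | 0.81 |
| 0.5 | 0.53 | 0.80 |
| 0.4 | 0.47 | 0.80 |
| 0.25 | 0.37 | 0.77 |

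The count loses discrimination steadily. It falls below 0.5 only at the ratios under one half.

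**Can a classifier rebuild the share from the listed features?** The overall share can be approximated from the negative count and total posts. The night and day shares cannot be obtained from those two plus one diurnal value on negative posts. Take 100 posts, 30 of them negative, with 60% of the negative posts at night, that is 18 at night and 12 by day:
- If 60 of all posts are at night: 18/60 = 30% and 12/40 = 30%.
- If 30 of all posts are at night: 18/30 = 60% and 12/70 = 17%.

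The three inputs are identical and the night-versus-day contrast is entirely different.

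**Mutual information.** With the Po = 0 rows removed, Po is constant and formula (4) is exactly 0. An assumed table (40, 10 for nonnegative and 20, 30 for negative posts, without and with emoji) gives 0.086 when all four cells are kept. Nonnegative posts are needed here too.

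**The case against.** Several counter-arguments carry weight.

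- The sentence that eliminates nonnegative posts belongs to the mutual-information step and is not stated for formula (3). A reader might infer that the study discards nonnegative posts altogether. The text does not support that: positive affect and sentiment scores are planned features. What stands is that timing and frequency are, separately, worded for negative posts.
- Formula (3) can be read as covering all posts, in line with the article's description of diurnal activity as activeness by day and night. That is a legitimate feature and should stay. On that reading, however, it says nothing about negative posts, which is what the section says it will time.
- Total posts are already listed, and the tree-based models under ML Modeling could partly recover the overall share. This is right and softens the predictive loss. Post time is listed too; were it coded as an all-posts hour profile, the night and day shares could in principle be pieced together, but the article states no such coding.
- A reader might infer that the model will be biased against depressed people. That does not follow. The classifiers are supervised and learn direction from labels, and no fixed rule equates more negative posts with higher risk.
- The evidence on volume is mixed. SM Engagement Analysis says people with clinical depression are on social media for longer. That is time rather than posts, but it warns against treating a fall in volume as settled.
- A condensed article may leave feature definitions to the full protocol. The point here is not missing detail: the quantities that are stated are the wrong ones for the stated purpose.

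**Conclusion.** The point holds in a limited form. Negative posts are timed and counted without being related to all posts. The diurnal value therefore either largely reflects posting time or carries no negativity, depending on which meaning of Po is used. The negative count does carry negativity, but mixed with volume. It can lose discrimination, and it reverses only if volume falls proportionally more than the negative share rises. The article supports the direction of that fall in one sentence and gives no size, so the AUC range of 0.67 down to 0.37 illustrates the mechanism and is not an estimate for this cohort.

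The supervised models may recover part of the loss for overall negativity. They cannot recover the night-versus-day negative share from the negative count, total posts and a negative-post diurnal value. Nor do they repair the descriptive aim in the Results section, which is reported directly and does not pass through a classifier.

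**What to change.** - Define Po once and use that definition in formulas (3) and (4).
- Keep nonnegative posts, including in the mutual-information table.
- Add for each participant the number of negative posts divided by all posts, overall and separately for night and day.
- Enter these alongside the diurnal activity value computed on all posts and the total number of posts, which is already listed.
- Do not interpret the raw negative count, or the hour distribution of negative posts alone, as negativity.

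The cost is a change of feature definition; the nonnegative posts should be in the Facebook file that participants upload. The drawback is that shares are noisy for people with few posts, more so once split by night and day. A minimum number of posts or shrinkage toward the overall mean should therefore be fixed in advance.

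### The mutual information formula assigned to the time-of-day question contains no time variable, so it cannot show whether post emotion or emoji use varies with time of day

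*Protocol article*

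**What the plan says.** All of this is in the Diurnal Activity section of the protocol article.

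- **Question and method.** The authors will consider how the emotion in a post and "the number of emojis used on a post are correlated with diurnal activity. For that, we will be using the formula for MI". The reason given is that MI combines a joint and a marginal probability.
- **What the joint probability is for.** It "will help investigate the relationship between the emotions in the posts and the number of emojis used". Time is not mentioned. A condition is attached: "if we work on the sentiments in the posts, then the number of emojis will be kept constant, and vice versa".
- **The formula.** The modified version, formula (4), begins "MI(Po,E) = ∑∑P(Po,E)e log (P(Po,E)e) / (P(Po)e × P(E)e". It has two arguments, Po and E.
- **Two descriptions of Po.** In words, Po "will indicate the posts written by an individual during nighttime". In the coding that follows, the authors "consider the values of both Po and E as binary 1" when the post is negative and emojis are used. Po=0 means nonnegative and E=0 means no emoji.
- **Cells removed.** Both Po=0 combinations are to be eliminated. The reason given also rules out E=0.
- **Where time appears.** Formula (3) is the number of posts at day d and hour h divided by a sum of such counts, with h running from 0 to 23. The section also says that time stamps of negative posts will be observed.

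**The concern.** MI measures the dependence between the two variables placed in it and nothing else. A question about time of day needs time as one of those variables. Here the two variables are emotion and emoji use, so formula (4) addresses whether emotion and emoji use go together, which is a different question from the one it was chosen to answer.

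The section's premise is that depressed people are most active at night. If formula (4) is reported as the relation with diurnal activity, its value will carry no information about that premise for emotion or for emojis, yet it will be labelled as if it did.

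**Working it through.** The plan gives no numerical MI result to reproduce, so the check asks whether formula (4), as coded, can respond to time of day.

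**Step 1: the variables.** From the coding in the section, Po ∈ {negative, nonnegative} and E ∈ {emoji, no emoji}. The formula is

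MI(Po,E) = Σ p(po,e) · log2[ p(po,e) / (p(po) · p(e)) ].

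The article does not give the base of the logarithm; base 2 (bits) is used here. No hour, day or day/night term appears.

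**Step 2: illustrative counts (assumptions, not from the article).** T is day/night. Rows are Po=1 and Po=0; columns are E=1 and E=0.

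| Set | Night | Day | Negative share, night vs day |
|---|---|---|---|
| A | [[100,100],[100,200]] | [[100,100],[100,200]] | 200/500 = 40% vs 200/500 = 40% |
| B | [[190,190],[20,100]] | [[10,10],[180,300]] | 380/500 = 76% vs 20/500 = 4% |
| C | [[100,100],[100,200]] | [[10,10],[180,300]] | 200/500 = 40% vs 20/500 = 4% |

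**Step 3: formula (4) on posts from all hours, A against B.** Both sets pool to [[200,200],[200,400]] out of 1,000. The cell proportions are 0.2, 0.2, 0.2 and 0.4, and both margins are 0.4 and 0.6.

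MI = 0.2·log2(0.2/0.16) + 2·0.2·log2(0.2/0.24) + 0.4·log2(0.4/0.36) = 0.0644 − 0.1052 + 0.0608 = 0.0200 bits in both sets.

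The measure with time separates them: MI(T;(Po,E)) is 0.0000 in A and 0.4671 in B. Most of the B value comes from negative posts:

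MI(T;Po) = 0.38·log2(0.38/0.20) + 0.12·log2(0.12/0.30) + 0.02·log2(0.02/0.20) + 0.48·log2(0.48/0.30) = 0.4523 bits.

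**Step 4: formula (4) on night posts only, A against C.** The night tables are identical, so MI(Po,E) is 0.0200 in both. MI(T;(Po,E)) is 0.0000 in A and 0.1546 in C. Restricting to night discards the daytime comparison that a time relation requires.

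**Step 5: the elimination rule.** With Po=0 removed, p(Po=1) = 1 and p(1,e) = p(e). Every term is then p(e)·log2[p(e)/p(e)] = 0, so MI(Po,E) = 0 for any data. Removing E=0 as well leaves one cell, and the value is again 0.

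**Step 6: formula (3).** It is indexed by day and hour but has no emoji term, and nothing links it to formula (4). The section assigns the question to MI, not to formula (3).

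**The case against.** **The nighttime definition of Po.** On this view the authors mean an emotion–emoji association within night posts, loosely described as a correlation with diurnal activity. That may well be what was intended, and the fault would then be mainly one of wording. It does not make formula (4) answer the sentence as written, because one time stratum cannot show a contrast (step 4). If Po were instead a night/not-night indicator, time would enter but emotion would leave, against the stated coding.

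**Time is handled elsewhere.** Time stamps of negative posts are to be observed, and formula (3) could describe their clustering by hour if Po there means negative posts. The text is unclear, since Po in formula (3) is also called the number of posts. This part stands: a reader might infer that night clustering of negative posts would go wholly unseen, and the article does not support that. Emoji use by hour remains uncovered.

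**Error rates.** A reader might infer that the plan would raise false diurnal signals at a high rate, or lose a stated amount of power. The article gives no hypothesis, test or alpha for MI; it is a descriptive quantity. Any such rate depends on invented inputs and on the reading taken. As an illustration, assume a user with 200 posts, 40% at night, no time relation, 30% negative posts, emojis in 20% of negative and 45% of other posts, and a likelihood-ratio test at 0.05. Formula (4) then signals in 94% of simulated runs on all posts, 59% on night posts only, and 0% with Po=0 eliminated. Under the text as written, the false signal cannot arise.

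**The kept-constant condition.** It is tempting to read this as forcing MI to zero. It can equally mean looking at sentiment within levels of emoji count, that is, stratification. It is unclear drafting, not proof of a null statistic.

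**Importance.** Textbox 1 lists the diurnal activity value as a model input but does not list MI, and the evaluation metrics do not depend on it. This also stands and limits the severity.

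**Conclusion.** The point holds in a limited form. With the article's own coding, formula (4) has no time variable, so it cannot show how emotion or emoji use relates to time of day, whether it is run on all posts or on night posts only. If the elimination rule is applied literally, it cannot show the emotion–emoji association either, because it equals 0 whatever the data.

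The structural result needs no assumptions beyond the stated coding. The values in bits (0.0200 from formula (4) in each comparison, against 0.0000 versus 0.4671 or 0.1546 with time included) rest on assumed counts and only illustrate it. No false-alarm rate or power loss can be attributed to this plan. The mismatch should be corrected, but it concerns one secondary feature family among many and does not bear on the main evaluation of the classifier.

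**What to change.** In the Diurnal Activity section:

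1. Define T as day/night (with stated cut-off hours) or as hour, taken from the post timestamp.
2. For the diurnal question, replace formula (4) by MI(negative;T) and MI(emoji;T). Alternatively, use each person's night-minus-day difference in the share of negative posts and in the share of posts with emojis.
3. Use posts from all hours and keep all four Po-by-E cells, deleting the elimination rule. Without this the replacement fails too: if only negative posts remain, MI(negative;T) is 0 for any data, and the same holds for MI(emoji;T) if only emoji posts remain.
4. Keep MI(negative;emoji) only as a separate emotion–emoji feature, labelled as such.
5. Give Po a single definition, and delete the kept-constant condition or restate it as stratification.

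If the authors want only the emotion–emoji association among night posts, they should restate the aim in those terms, drop the claim about diurnal activity, and still keep all four cells.

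The cost is a few sentences of text and one recomputed feature family. Timestamps are already to be used, so no new data are needed.

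### The Diurnal Activity text says emoji number or sentiment is held constant while mutual information measures their association; this conflicts with formula (4) and gives zero if applied as a restriction

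*Protocol article*

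**What the plan says.** All the relevant text is in the protocol article, Methods, Text and Behavior Analysis, Diurnal Activity.

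- **Purpose.** MI is chosen because it contains both joint and marginal probabilities. The joint probability "will help investigate the relationship between the emotions in the posts and the number of emojis used, applying a condition". The condition follows: "if we work on the sentiments in the posts, then the number of emojis will be kept constant, and vice versa".
- **Marginals.** The next sentence says that marginal probability lets one feature be extracted at a time, and glosses this as "the features will be independent of one another".
- **Formula (4).** "MI(Po,E) = ∑∑P(Po,E)e log (P(Po,E)e) / (P(Po)e × P(E)e", a double sum over Po and E.
- **Meaning of E.** The condition speaks of the number of emojis. The text before formula (4) says that E "will indicate the types of emojis used by that individual". The coding after it is binary: "We will consider the values of both Po and E as binary 1 (ie, Po=1 and E=1" for negative posts with emojis, and both are 0 "if the posts are “nonnegative” and no emojis are used in the post".
- **Cells.** The two mixed cells are listed as well ("There are other combinations as well, that is, Po=0 and E=1", then Po=1 with E=0). The plan then eliminates both cells with Po=0, explaining that nonnegative posts and zero emojis will not be dealt with.

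**The concern.** MI measures how far the joint distribution of two variables departs from the product of their marginals. It has something to measure only when both variables vary. The condition fixes one of the two variables whose association is being studied. Once one is fixed, only the conditional distribution of the other remains, and that distribution says nothing about association.

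The remark about independent features adds to the confusion. Taking a marginal does not make features independent. Independence is the reference against which MI compares the joint distribution.

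If an analyst applied the condition as a restriction, each participant would receive the same MI of zero. An apparent absence of any emotion-emoji relationship would then come from the rule and not from the data. The section Comparison With Previous Work names emoji use among the study's distinctive parameters, so this analysis deserves a valid definition.

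**Working it through.** The plan states no MI value, so there is no figure to reproduce. The check applies formula (4) to an illustrative table; the proportions are assumptions.

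**Inputs (assumed).** P(Po=1) = 0.35; P(E=1) is 0.30 among negative posts and 0.60 among nonnegative posts; E is binary (emojis used or not).

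**1. Both variables free.**

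| | E=0 | E=1 | Sum |
|---|---|---|---|
| Po=0 | 0.65 × 0.40 = 0.260 | 0.65 × 0.60 = 0.390 | 0.65 |
| Po=1 | 0.35 × 0.70 = 0.245 | 0.35 × 0.30 = 0.105 | 0.35 |
| Sum | 0.505 | 0.495 | 1 |

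Each term is P(Po,E) × log2[P(Po,E) / (P(Po) × P(E))]. In reading order the four terms are −0.087, +0.108, +0.115 and −0.076, so MI = 0.060 bits. With emoji use of 20% versus 70% in place of 30% versus 60%, the same calculation gives 0.173 bits.

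**2. E restricted to 1.** P(E=1) becomes 1, and P(Po=0) = 0.390 / 0.495 = 0.788. The ratio inside the log is 0.788 / (0.788 × 1) = 1, and likewise for Po=1. Every log is 0, so MI = 0. The same holds with E restricted to 0 or Po restricted to either value, for any table.

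**3. One variable fixed level by level, then recombined.** P(Po=0 | E=1) × P(E=1) = 0.788 × 0.495 = 0.390, the original cell. Doing this for each cell rebuilds the table of step 1, and MI is again 0.060 bits.

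**4. Emoji number fixed, E meaning type.** Suppose every post has one emoji of one of two types, with assumed counts of 5 and 30 in nonnegative posts and 25 and 10 in negative posts. MI is 0.1787 in natural-log units, or 0.1787 / 0.6931 = 0.258 bits. Fixing the number does not fix the type.

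**5. The elimination of the Po=0 cells.** If those posts are removed and the rest rescaled, Po=1 throughout, P(E=1) = 0.30 and each ratio is 1, so MI = 0. If only the two Po=0 terms are dropped while the full-table marginals are kept, the remainder is 0.115 − 0.076, about 0.040 bits. That is a partial sum and not an MI.

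**The case against.** The strongest reply is that the sentence is loosely worded and does not specify a restriction. It gives no value at which emojis are fixed and does not say that posts with other values are excluded. The words about the reverse case suit an analyst who takes one variable at a time to fill the table, and the plan goes on to list all four combinations. Step 3 shows that this reading returns the ordinary MI. The quantity held constant is also the number of emojis, whereas E is first introduced as type.

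These points stand, and they rule out a stronger claim that a reader might infer: that MI is zero for every participant even when all four cells of formula (4) are kept. Four populated cells mean that neither variable is constant.

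A reader might also infer from the independence remark that the plan sets the joint probability equal to the product of the marginals. It does not. Formula (4) keeps the joint as a separate term, and the remark is a poor description of the marginals only.

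Nor do the documents show that a model input is lost. The textbox of data variables under Principal Findings lists a diurnal activity value but no MI feature, and emoji counts enter separately among the post-centric behaviors.

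The objection does not rescue the sentence itself. On the level-by-level reading the condition changes nothing. On the restriction reading, which the later decision not to deal with nonnegative posts and zero emojis makes plausible, the measure is degenerate.

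**Conclusion.** The concern holds as a conflict between the stated condition and the definition of MI in formula (4). Under the binary coding of Po and E, applying the condition as a restriction gives MI = 0 for any data. In the assumed tables this replaces 0.060 or 0.173 bits; those two figures depend on the assumed proportions, while the zero does not. Zero is not established under the other readings of the sentence.

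The clearer source of a zero is the elimination of both Po=0 cells: once those posts are removed and the probabilities rescaled, MI is zero whichever way the hold-constant sentence is read. The two defects need separate correction, because restoring the cells alone would leave an instruction that can still be carried out as a restriction. The three descriptions of the emoji variable (number, type, used or not used) make the outcome depend on the analyst's interpretation. This should be corrected before the emotion-emoji analysis is run; it does not bear on the rest of the modeling plan.

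**What to change.** In the Diurnal Activity subsection:

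1. Delete the hold-constant condition and the wording that marginals make features independent.
2. Define E in one way, as number, type, or used/not used, and keep that definition in the text, the coding and formula (4).
3. With the binary coding, estimate P(Po,E) from each participant's full cross-table of posts, negative or nonnegative by emoji or no emoji. Restore the two Po=0 cells and take the marginals as the row and column sums of that table.
4. If day versus night is to be controlled for, stratify on time of day as a third variable and compute MI within each stratum, leaving Po and E free.

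The cost is a few sentences of wording. The cross-table comes from posts that the study already collects, so no new data and no change to recruitment are needed.
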